### Data analysis

This study will summarize patient disposition, demographic and other baseline characteristics, study drug exposure, safety and efficacy. Statistical analyses will be performed using R, version 3.5.0 (R Foundation for Statistical Computing, Vienna, Austria). Continuous variables will be summarized descriptively based on mean (Mean), standard deviation (SD), median (Median) and maximum (Max) and minimum (Min) values, and comparisons of differences between groups will be based on whether the data meet a normal distribution with a two independent samples t-test or wilcoxon nonparametric test. The categorical variables will be summarized descriptively based on the number of subjects in each category and their corresponding percentage share using the chi-square test, and the Fisher's exact test will be used to analyze the differences between groups if necessary. Kaplan–Meier curves and log-rank test will be used to estimate hospital survival in patients in both arms.

In addition, intention to treat analyses which will include all participants randomly assigned to the study arms regardless of their loss to follow-up or compliance will be implemented. Per-protocol analyses, which include all participants with complete data sets, will also be performed for primary and secondary outcomes. In case of missing data, multiple imputation will be calculated.

An interim analysis will be conducted when the set reaches 50% of the proposed number of patients; if the primary endpoint has been reached and differences exist, the data safety monitoring board will discuss and vote on whether to allow early termination of the study. Unless otherwise specified, α = 0.05 (two-sided test) and *p* < 0.05 was defined as statistically significant.

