### Outcomes

The primary outcome will be the difference of Sequential Organ Failure Assessment (SOFA) score on POD 4 compared to baseline (on POD1 before MP administration).

Secondary outcomes will be in-hospital mortality, days of ICU stay; days of hospital stay; duration of mechanical ventilation; tracheotomy; continuous renal replacement therapy; postoperative infection; inflammatory markers on POD 1, 2 and 3; composite endpoint (in-hospital morbidity and mortality or ICU stay over 30 days or tracheotomy).

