## Statistics

### Sample size

In this study, the SOFA score will be monitored continuously for 4 days after surgery. Our primary hypothesis is that the reduction in SOFA score of patients who will be treated with GC postoperatively would be greater than that in those treated with normal care. Based on our previous study, a decline of 2.87 ± 1.69 between the baseline SOFA score on POD1 and the one on POD 3 was observed in our patients [17]. Assuming a 25% increase in the reduction of the SOFA score in the GC group, a test level of α = 0.1 (bilateral), and a test efficacy of (1-β) = 0.9, it is expected that 96 cases are needed in each group, for a total of 192 cases. An estimate of a 10% dropout rate in these groups indicates that a sample size of 212 cases will be required.

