### Subgroup analyses

The effect of the treatment among different subgroups: (1) gender, (2) diabetes, (3) The European System for Cardiac Operative Risk Evaluation (EuroSCORE) II, (4) Cardiopulmonary Bypass (CPB) duration, (5) age, (6) high sensitivity C-reactive protein on POD 1 and (7) SOFA on POD 1 will be analyzed. Stratified analysis using a logistic regression or Cox proportional hazards model, as applicable, will be performed. By adding a product term to the model that already contains the treatment and the subgroup factor, the interaction between each subgroup factor and the treatment group will be tested.

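### The primary SOFA change is tested by an unadjusted t-test or Wilcoxon test chosen on a normality check; one pre-specified linear model adjusted for POD 1 SOFA would fix the estimand and usually gain precision

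*Protocol article*

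**What the plan says.** The Outcomes section defines the primary endpoint: "The primary outcome will be the difference of Sequential Organ Failure Assessment (SOFA) score on POD 4 compared to baseline (on POD1 before MP administration". Under Sample size, the hypothesis is that "the reduction in SOFA score of patients who will be treated with GC postoperatively would be greater" than under normal care. The planning figures there are a mean and an SD: "a decline of 2.87 ± 1.69 between the baseline SOFA score on POD1 and the one on POD 3 was observed in our patients". The effect is set as a proportion of that mean: "Assuming a 25% increase in the reduction of the SOFA score in the GC group".

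The only between-group method for continuous variables is under Data analysis. Groups are compared "based on whether the data meet a normal distribution with a two independent samples t-test or wilcoxon nonparametric test". That section names no covariate and no linear model, and it sets no separate rule for the primary outcome.

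The Subgroup analyses section lists seven factors, one of which is SOFA on POD 1. It states: "Stratified analysis using a logistic regression or Cox proportional hazards model, as applicable, will be performed". Interaction is tested by adding a product term to the model.

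**The concern.** There are two linked weaknesses and one smaller gap.

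- **The estimand is not fixed.** A t-test concerns a difference in means; a Wilcoxon test concerns a shift in ranks. If a normality check on the trial data picks between them, the quantity reported and its p-value depend on the data. SOFA change is a bounded whole-number score, so a normality check may well fail at about 100 patients per arm even where a comparison of means would be sound. The trial would then test something other than the mean difference on which it was sized.
- **The baseline is recorded but not used as a covariate.** Subtracting POD 1 SOFA gives it a fixed weight of one. A linear model estimates that weight and generally leaves less residual variance. Randomisation is in blocks of 4 with no stratification stated, so chance imbalance in baseline severity is not limited by design.
- **No named model suits a subgroup test on the primary outcome.** Logistic and Cox models do not fit a change in SOFA unless it is dichotomised.

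At stake are a primary result whose form is settled after the data are seen, and precision that could be had without extra patients.

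**Working it through.** **Inputs from the protocol (Sample size, Data analysis).** Control-arm decline 2.87, SD 1.69, observed from POD 1 to POD 3; effect 25% of the decline; 96 per arm; power 0.90; two-sided alpha 0.10 for sample size and 0.05 for analysis unless otherwise specified.

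**Assumptions, not in the protocol.** The correlation r between POD 1 and POD 4 SOFA; the ratio k = SD(POD 4) / SD(POD 1); and that the SD of change to POD 4 is also 1.69. All power figures use the normal approximation.

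**Step 1: reproduce the plan.** Effect = 0.25 × 2.87 = 0.7175. Per arm, n = 2 × [1.69 × (1.645 + 1.282) / 0.7175]² = 95.02, rounded up to 96. The stated figure is reproduced, and it is for an unadjusted comparison of mean change.

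**Step 2: power of the unadjusted t-test.** Noncentrality = 0.7175 / (1.69 × √(2/96)) = 2.941.

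- Alpha 0.10: Φ(2.941 − 1.645) = 90.3%.
- Alpha 0.05: Φ(2.941 − 1.960) = 83.7%. Reaching 90% would take 117 per arm (unrounded 116.59).
- Wilcoxon on normal data, relative efficiency 0.955, alpha 0.05: about 82.0%.

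**Step 3: variance after adjustment.** With the baseline variance set to 1, the change score has variance 1 + k² − 2rk, and the baseline-adjusted residual has variance k²(1 − r²). The first minus the second is (1 − rk)², which is never negative. In large samples the adjusted analysis is therefore never less precise, and the gain vanishes when rk = 1. With equal SDs (k = 1) the ratio of adjusted to change-score variance is (1 + r)/2.

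**Step 4: power at 96 per arm with adjustment, k = 1.** Divide 2.941 by the square root of the ratio.

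| r | Variance ratio | Power, alpha 0.05 | n per arm for 90%, alpha 0.05 | Power, alpha 0.10 |
|---|---|---|---|---|
| unadjusted | 1.00 | 83.7% | 117 | 90.3% |
| 0.3 | 0.65 | 95.4% | 76 | 97.7% |
| 0.5 | 0.75 | 92.5% | 88 | 96.0% |
| 0.6 | 0.80 | 90.8% | 94 | 95.0% |
| 0.7 | 0.85 | 89.1% | 100 | 93.9% |
| 0.8 | 0.90 | 87.3% | 105 | 92.7% |

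For 90% at alpha 0.05 with 96 per arm, the ratio may be at most 96 / 116.59 = 0.823, so r may be at most 2 × 0.823 − 1, about 0.65.

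**Step 5: unequal SDs, alpha 0.05.** For k = 1.2 and r = 0.7 the ratio is 1.44 × 0.51 / (1 + 1.44 − 1.68) = 0.7344 / 0.76 = 0.966, and power is 84.9%.

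| k | r = 0.3 | r = 0.5 | r = 0.7 | r = 0.8 |
|---|---|---|---|---|
| 0.8 | 98.6% | 97.3% | 96.0% | 95.7% |
| 1.0 | 95.4% | 92.5% | 89.1% | 87.3% |
| 1.2 | 92.1% | 88.3% | 84.9% | 83.8% |

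The gain thus runs from nothing to well over ten points, depending on two quantities that the protocol does not report.

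**The case against.** The strongest reply is that the planned analysis is valid and matches its sample size. Under randomisation a two-sample comparison of change is unbiased with correct type I error, and 96 per arm is the right number for that test at the alpha used to size it. Subtracting POD 1 SOFA already uses the baseline in part. This stands. A reader might infer that omitting the covariate biases the result; it does not. Chance imbalance affects the estimate in the single trial that is run, not its average over repeated randomisations.

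A reader might also infer that the choice of test costs the trial its planned power, and that adjustment would win it back. Neither follows. The fall from 90.3% to 83.7% comes entirely from moving from alpha 0.10 to 0.05, and Step 4 shows that 90% is not regained at r = 0.7 or 0.8 even with equal SDs.

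A third tempting reading is that all seven interaction tests lack a valid model. The Subgroup analyses section does not name the outcome, and it says the models apply where applicable. Logistic and Cox models can serve the binary and time-to-event outcomes. The gap exists only if the primary outcome is analysed by subgroup.

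Finally, covariate adjustment is often left to an analysis plan, which is not shown, and the quoted rule is generic. But the rule is the only one for continuous variables and the primary outcome is one of them. The article therefore states a method, and the point is that a better one should replace it.

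**Conclusion.** The point holds as an improvement to a stated method, not as an error that invalidates the trial. The primary test, and with it the quantity estimated, depends on a normality check although the trial was sized on a mean difference. The baseline is collected but not used as a covariate.

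The direct power cost of a switch to Wilcoxon is modest, under two points on normal data. The benefit of adjustment at alpha 0.05 is roughly 4 to 12 points for correlations of 0.8 to 0.3 with equal SDs, but about one point at r = 0.7 with a POD 4 SD 1.2 times the baseline SD, and almost none at r = 0.8 with that SD ratio. These sizes rest on the assumed r and k, and on carrying the POD 3 SD over to POD 4. That fixing one analysis in advance is better does not rest on them.

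Adjustment may offset the shortfall from 90% in part or in full, but it does not settle which alpha governs the primary test.

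**What to change.** - Under Data analysis, name a single primary analysis: a linear model of POD 4 SOFA (or of the change) on treatment and pre-drug POD 1 SOFA, with robust standard errors, reporting the adjusted mean difference and its 95% CI. Drop the normality check as a decision rule for this outcome and keep Wilcoxon as a sensitivity analysis only.
- Under Subgroup analyses, state which outcomes are examined. For the primary outcome, use the same linear model with a treatment-by-factor term. Keep logistic and Cox models for binary and time-to-event outcomes.
- Separately, reconcile the alpha of 0.10 under Sample size with the 0.05 under Data analysis, and restate the power. If credit is taken for adjustment, take r and k from the sponsor's earlier cohort, if its data allow.

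The first two items need only new wording in the protocol and analysis plan, with no extra data or patients, because POD 1 SOFA is already needed to form the change score. They should be settled before any outcome data are compared by arm, including at the interim analysis.

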### Overview

All patients with aTAAD undergoing surgery will be screened for study eligibility. Upon enrollment, eligible patients will be randomized 1:1 to one of the two treatment arms (i.e. GC or normal treatment) (Fig. 1). Data will be collected until hospital discharge or death.

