### Data collection and storage

Blinded trial investigators will enter the baseline characteristics, process variables, and outcome data from the patient files into web-based case report forms (Electronic Data Capture System) from POD 1 to POD 4, and follow up at discharge from hospital. Calculation of the SOFA score will be done by the on-duty physician. Personal information about potential and enrolled participants will be collected and maintained. The initial of patient’s full name will be used instead of the real name to identify certain patients. In addition, during the study period, a unique identification number will be used as the dominant way to follow certain patients to protect confidentiality. If necessary, information stored in the electronic patient record will be used for follow-up and patients or their surrogates will be contacted directly if additional data is needed. Data will be stored in a third-party system and the trial investigators have full access to it.

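### Kaplan-Meier and log-rank for hospital survival, run in the standard way with follow-up ending at discharge, would overstate in-hospital death and tie the test to length of stay

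*Protocol article*

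**What the plan says.** The Data analysis section of the protocol article states: "Kaplan–Meier curves and log-rank test will be used to estimate hospital survival in patients in both arms". Two other sections set the end of observation. The Overview says "Data will be collected until hospital discharge or death", and Data collection and storage has data entered "from POD 1 to POD 4, and follow up at discharge from hospital". That section also allows records to be consulted or patients contacted if more data are needed, but it plans no vital status after discharge. No fixed day for survival, no censoring rule and no competing-risk method is given.

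The Outcomes section lists mortality beside the durations of stay: "Secondary outcomes will be in-hospital mortality, days of ICU stay; days of hospital stay; duration of mechanical ventilation". For categorical outcomes, Data analysis names the chi-square test and adds that "the Fisher's exact test will be used to analyze the differences between groups if necessary". The default level is two-sided 0.05. Subgroup analyses offers logistic regression or a "Cox proportional hazards model, as applicable", without naming the outcome.

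**The concern.** Kaplan-Meier requires that patients censored at a given day have the same later risk of the event as those still under observation. A patient discharged alive has recovered enough to leave and can no longer die in hospital. If discharge is handled as ordinary censoring, two things follow.

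- The curve describes what would happen if nobody could leave, so it overstates in-hospital death in both arms, whatever the treatment does.
- The log-rank test compares deaths per day among patients still in hospital, not the chance of dying in hospital. An arm whose patients leave sooner has fewer survivors in the denominator, and so looks worse at equal mortality.

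Length of stay is itself a secondary outcome, so the trial is asking whether treatment shifts the censoring times. The report could then carry two mortality tests that disagree, with no rule for which governs.

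**Working it through.** **The plan's own figures.** The article gives no figure for the survival analysis. Only the arm size is needed from the sample-size section, and it reproduces. The effect is 0.25 × 2.87 = 0.7175, and 2 × [1.69 × (1.645 + 1.282) / 0.7175]² ≈ 95.0, rounded up to 96 per group. Then 192 × 1.1 = 211.2, rounded up to 212. With allocation 1:1 ("eligible patients will be randomized 1:1 to one of the two treatment arms") that is 106 per arm.

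**Assumed inputs.** The article gives no mortality or length of stay, so ranges are used: in-hospital mortality p of 5%, 10%, 15% and 20%; mean time to death 8 or 15 days; mean stay of survivors 18 days in one arm and 18, 15, 12 or 9 in the other. Times are gamma distributed. There were 5,000 simulated trials per scenario, so the Monte Carlo standard error at 5% is √(0.05 × 0.95 / 5000) = 0.3 percentage points.

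**Step 1: what each estimator targets.** Let f_D and S_D be the density and survivor function of death times among those who die in hospital, F_D = 1 − S_D, and S_L the survivor function of discharge times among survivors.

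- Discharge censored: hazard = p·f_D / [p·S_D + (1 − p)·S_L].
- Discharged patients kept at risk: hazard = p·f_D / [p·S_D + (1 − p)], which integrates to cumulative incidence p·F_D(t).

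S_L falls below 1 as patients go home. The first hazard is therefore the larger, and it depends on discharge timing. The second does not.

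**Step 2: the curves at day 30, 18-day mean stay.**

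| True in-hospital mortality | 1 − KM | True cumulative incidence |
|---|---|---|
| 5% | 6.5% to 7.9% | 4.4% to 4.9% |
| 10% | 13.0% to 15.0% | 8.7% to 9.7% |
| 15% | 19.8% to 22.1% | 13.2% to 14.9% |
| 20% | 25.9% to 28.5% | 17.5% to 19.7% |

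The ranges span the two mean times to death. The gap grows with time. At 10% mortality it is small at day 14 (8.9% against 8.3%, or 6.4% against 5.9%) and large at day 60 (19.8% to 58.7% against about 9.8% to 9.9%), when few patients remain.

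**Step 3: the log-rank test, with equal mortality and equal death times in both arms.**

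| Mean stay of survivors, by arm | Type I error, discharge censored |
|---|---|
| 18 and 18 days | 4.2% to 5.3% |
| 18 and 15 days | 5.4% to 9.1% |
| 18 and 12 days | 8.3% to 27.6% |
| 18 and 9 days | 17.5% to 59.5% |

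With discharged patients kept at risk, type I error is 4.2% to 5.4% in every scenario.

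The excess rejections go against the arm discharged earlier. At 10% mortality and 18 against 12 days, 10.3 of 10.9 percentage points do so when mean time to death is 8 days, and 22.0 of 22.1 when it is 15 days.

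**The case against.** The strongest reply is that the article never says discharged patients are censored. It names an estimator and says when data collection ends. For survival in hospital, a discharged patient's outcome is known, and carrying that patient forward as event-free is still Kaplan-Meier with log-rank and needs no new data. A full analysis plan, not shown here, may say so. This stands in part: the error is the default result of the stated method and end of follow-up, not a stated rule. It does not remove the point, because nothing in the article steers the analyst away from that default.

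It is also fair that in-hospital mortality can already be compared as a proportion, that every input above is assumed, and that the distortion of the test vanishes when stay is equal. All of this stands. The overstated curves, however, need no difference between arms.

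Three stronger readings are tempting and not supported:

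- **A definite size of false harm.** With constant hazards, 10% mortality and mean stays of 15 and 12 days, the death hazards are 0.10/15 and 0.10/12 per day, a ratio of 1.25. A reader might call this an apparent 25% harm at equal mortality. That model also brings deaths earlier in the shorter-stay arm, so it is not a clean null. With about 212 × 0.10 = 21 deaths, the log-rank test rejected in only 8.2% of simulated trials of that scenario.
- **The Cox subgroup models share the fault.** The Subgroup analyses section does not tie the Cox model to mortality.
- **The trial's mortality conclusion is invalid.** The comparison of proportions is unaffected.

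**Conclusion.** The point holds in a limited form. If survivors are censored at live discharge, as the stated method and end of follow-up imply by default, the hospital-survival curves overstate in-hospital death in both arms, and the log-rank test can reject too often when the arms differ in time to discharge. At an assumed 10% mortality the day-30 excess is roughly 3 to 6 percentage points (13.0 − 9.7 = 3.3; 15.0 − 8.7 = 6.3). A 3-day difference in mean stay does little harm to the test, and a 6-day difference can do a good deal. These sizes rest wholly on assumed mortality, stay and shape of the time distributions.

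The effect is confined to one secondary outcome. The primary SOFA comparison, the sample size and the interim look at the primary endpoint are untouched. The change should be made, but the trial does not depend on it.

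**What to change.** In Data analysis:

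1. Name the proportion dying in hospital, with risk difference and 95% confidence interval, as the governing mortality analysis.
2. Replace Kaplan-Meier and log-rank by cumulative incidence curves (Aalen-Johansen) with live discharge as a competing event, compared by Gray's test. Alternatively, keep Kaplan-Meier and log-rank and state that patients discharged alive remain in the risk set as event-free to a fixed, named horizon.
3. Apply the same rule to a Cox model only if one is used for in-hospital mortality.

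The cost is a sentence or two in the analysis section and standard R packages. No new data are needed, since death in hospital and length of stay are already collected.

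### The efficacy interim at 50% has no adjusted boundary: if p < 0.05 is used at both looks, the two-sided type I error can reach 8.3% instead of 5%

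*Protocol article*

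**What the plan says.** The Data analysis section of the protocol article states: "An interim analysis will be conducted when the set reaches 50% of the proposed number of patients". It continues: "if the primary endpoint has been reached and differences exist, the data safety monitoring board will discuss and vote" on early termination. The trigger is therefore a difference on the primary endpoint, the change in SOFA score from postoperative day 1 to day 4, and a board vote follows. The next sentence gives the only level for analyses: "Unless otherwise specified, α = 0.05 (two-sided test", with p < 0.05 counted as significant. The article gives no interim p-value, stopping boundary, spending function or adjusted final level.

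The Sample size section uses another level, "a test level of α = 0.1 (bilateral", with "a test efficacy of (1-β) = 0.9". It arrives at 96 per group, 192 in total, raised to 212 for dropout. It mentions no interim look.

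**The concern.** The same endpoint is tested twice, and the first test can end the trial. If both tests use the full level, a trial of an ineffective treatment has two chances to produce a positive result, and the overall false-positive rate exceeds the level stated.

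An early stop on a loose threshold also biases the estimate upwards, because only interim results large enough to cross the threshold lead to a stop. A positive claim could then carry a higher error rate than reported and an exaggerated effect.

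This goes beyond a detail left to another document. The article states a trigger and a default level which together, read literally, give an unadjusted rule.

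**Working it through.** **Inputs.** From the Sample size section: "a decline of 2.87 ± 1.69 between the baseline SOFA score on POD1 and the one on POD 3 was observed", so the SD is 1.69; and "Assuming a 25% increase in the reduction of the SOFA score in the GC group", so the difference is 0.25 × 2.87 = 0.7175 points. Allocation is 1:1. From the Data analysis section: one interim at 50%, and two-sided 0.05 by default.

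**Step 1: the plan's own figure.** n per arm = 2 × SD² × (z for alpha + z for power)² / difference².
- Two-sided 0.10, 90% power: 2 × 1.69² × (1.645 + 1.282)² / 0.7175² = 95.02, rounded up to 96. This reproduces the stated 96 per group as a design with a single look.
- Two-sided 0.05, 90% power: 2 × 1.69² × (1.960 + 1.282)² / 0.7175² = 116.6, rounded up to 117 per arm before dropout.

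**Step 2: type I error over two looks.** Under no effect, the statistics Z1 (interim) and Z2 (final) are bivariate normal with correlation √0.5 = 0.707. Overall error = 1 − P(|Z1| < c1 and |Z2| < c2).

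| Interim level | Final level | Overall two-sided error |
|---|---|---|
| 0.05 | 0.05 | 8.31% |
| 0.05 | 0.10 | 12.5% |
| 0.10 | 0.05 | 12.5% |
| 0.10 | 0.10 | 16.0% |

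Simulated t-tests under the null (200,000 trials each), with both looks at 0.05, gave 8.31% at 48 then 96 per arm and 8.25% at 53 then 106 per arm. Timing matters little: the error is 8.5% at 45% information and 8.1% at 55%.

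**Step 3: the interim under the planned effect, 48 per arm.**
- Standard error = 1.69 × √(2/48) = 0.345.
- Expected Z = 0.7175 / 0.345 = 2.080.
- Chance of p < 0.05 in favour of treatment = P(Z > 1.960 − 2.080) = 0.548.
- Mean estimate given that result = 0.7175 + 0.345 × φ(−0.120) / 0.548 = 0.967, where φ is the standard normal density. The ratio 0.967 / 0.7175 is 1.35, an overstatement of about 35%.
- With 53 per arm (half of 212, no dropout) the figures are 59%, 0.934 and about 30%.

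**Step 4: boundaries that preserve 0.05 with one look at 50%.**

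| Boundary | Interim p | Final p | Overall error |
|---|---|---|---|
| Lan-DeMets, O'Brien-Fleming type (bounds 2.963 and 1.969) | 0.003 | 0.049 | 5.00% |
| O'Brien-Fleming | 0.0052 | 0.0480 | 5% |
| Pocock | 0.0294 | 0.0294 | 5% |
| Haybittle-Peto | 0.001 | 0.05 | 5.02% |

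**Step 5: power at 96 per arm.** The standard error is 1.69 × √(2/96) = 0.2439 and the expected Z is 0.7175 / 0.2439 = 2.941.
- Fixed design, two-sided 0.10: P(Z > 1.645 − 2.941) = 0.903.
- Fixed design, two-sided 0.05: P(Z > 1.960 − 2.941) = 0.837.
- With the Lan-DeMets bounds: 0.835, a loss of 0.14 percentage point against 0.837.

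**The case against.** The strongest reply is that the article does not make p < 0.05 an automatic stopping rule. The board discusses and votes, the trigger has no number attached, and the words that introduce the 0.05 default leave room for a separate interim level. A boundary may also stand in an analysis plan or board charter that is not shown. Part of this stands. A reader might infer that the false-positive rate simply is 8.3%, but that needs every interim p < 0.05 to lead to a stop or a positive claim, which the text does not say. The 35% overstatement carries a similar condition. Nor does the article prove that no adjustment exists elsewhere. It does print a default that covers both looks, and discretion without a boundary leaves the error rate uncontrolled.

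A second reply is that the 5% reference is itself unsettled. If the primary test is meant to be held to 0.10, two looks at 0.05 (8.3%) stay below it. This also stands, and it is why the two levels must be reconciled first. It does not remove the problem, because reusing whichever level is chosen unadjusted at both looks exceeds that level.

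A reader might also infer that the board would stop on SOFA alone, without regard to mortality or infection. The article does not support that: these outcomes are collected, and nothing keeps them from the board.

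**Conclusion.** The point holds as a ceiling. As written, the plan permits two unadjusted tests of the primary endpoint, with an overall two-sided type I error of up to 8.3% against a nominal 5%, or up to 16.0% against 10% if 0.10 is used at both looks. The actual rate lies between the nominal level and the ceiling, depending on how the board votes. The calculation assumes a look at half the information, the same level at both looks and approximately normal test statistics.

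The interim threshold would not be a rare event. If the planned effect is real, p < 0.05 in favour of treatment is more likely than not at 48 per arm, and the estimate reported after such a result would on average be about a third too large.

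**What to change.** Before any interim data are seen:

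1. Settle one two-sided alpha for the primary endpoint, 0.05 or 0.10, and use it in both the Sample size and Data analysis sections.
2. State a boundary that preserves it. For 0.05 overall, one choice is a Lan-DeMets O'Brien-Fleming-type boundary: p < 0.003 at 50% and p < 0.049 at the final analysis. Other alpha-preserving boundaries are equally acceptable.
3. State that an interim p < 0.05 is not by itself the stopping criterion.

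The boundary takes one or two sentences in the protocol, analysis plan and board charter. It costs about 0.1 percentage point of power and makes an early stop less likely: under the planned effect, the chance of crossing at 48 per arm falls from 55% to P(Z > 2.963 − 2.080) = 19%.

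The choice of alpha has a separate and larger cost. If 0.05 is chosen, power at 96 per arm is about 84% and should be restated, or the size revised: 90% power needs 117 per arm before dropout and before any interim adjustment.
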